## Exploratory Tests and Observations

### Collection of Blood for Generation of iPS Cells and in vitro Efficacy Testing of Sirolimus (Optional)

The principal investigator or subinvestigator will collect blood to be used for generation of iPS cells between V1 and V12. Generation of iPS cells and in vitro efficacy testing using PDS-specific iPS cells will be performed at Keio University School of Medicine.

Prior to performing this test, the subjects or their legally acceptable representatives will be provided information for consent separately from the informed consent for participation in the trial. Blood sample collection and in vitro efficacy testing will be carried out only for those who consent to the test.

### Thyroid Ultrasound

The principal investigator or subinvestigator will perform thyroid ultrasound during the screening phase (V0), Phase II (V5 and V12), and at discontinuation.

### MRI (optional)

The principal investigator or subinvestigator will perform an MRI scan of the inner ear during Phase II (V5 and V12) and at discontinuation for subjects aged 16 or older with consent to the test, four hours after intravenous injection of contrast media. The allowable visit windows are to be within four weeks before V5, four weeks after V12, and four weeks after discontinuation.

### Cytology Test (optional)

The principal investigator or subinvestigator will perform a cytology test of thyroid for an exhaustive gene expression analysis in Phase II (V5 and V12) and at discontinuation for subjects with consent to blood collection for cytology test. This study will be performed only for subjects with consent based on prior explanation to the subjects or their legally acceptable representatives. As soon as the specifics of the exhaustive gene manifestation mapping are established, an “informed consent form concerning exhaustive gene manifestation mapping using thyroid cytology test” will be prepared and the information will be provided to obtain consent.

## Adverse Events

### Definition of Adverse Events

An adverse event in this trial refers to any untoward medical occurrence in a subject from initial administration of investigational products (V1) to follow-up observations (V13). The event may not necessarily have to have a causal relationship with administration of investigational products in this trial. An adverse event can therefore be any unfavorable and unintended sign (including an abnormal laboratory finding, for example), symptom, or disease temporally associated with the use of a medicinal product, whether considered related to the medicinal product or not.

Exacerbation of the primary disease, including episodes, will not be regarded as an adverse event, with the exception of cases in which causal relationship with the investigational products cannot be ruled out.

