### Assessment of Adverse Events

The items listed below will be examined and recorded on the electronic case report forms with regard to adverse events that occur from the initial administration of investigational products (V1) to follow-up observations (V13).

If a diagnosis is settled based on signs or symptoms, the diagnosis rather than the signs or symptoms should be recorded. With regard to vital signs and clinical test measurements, changes from conditions before administration of investigational products should be assessed to determine whether the changes are clinically significant. An abnormal change that is considered clinically significant is to be counted as an adverse event. An abnormal change that is relevant to symptoms and signs already recognized as an adverse event, shall not be required to be newly reported as a separate adverse event.

・Name of the adverse event

・Date of occurrence

・Severity

・Seriousness

・Actions taken (administration of investigational products or other actions)

・Outcome and date of outcome confirmation

・Causal relationship with the investigational products

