### Definition of Serious Adverse Events

Seriousness of adverse events is categorized as follows:

1) Non-serious: cases other than 2)

2) Serious: events for which any of the items from a) to g), below, apply.

a) Death

b) Cases that might result in death

c) Any case that requires hospitalization for treatment or prolongs the duration of hospitalization

d) Disability

e) Cases that might result in disability

f) Other medically serious condition for which seriousness is equivalent to a) to e), above

g) Any congenital diseases or abnormalities in the next generation

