### Reporting of Serious Adverse Events

If a serious adverse event is observed, the principal investigator or subinvestigator shall take necessary measures such as treatment for the subject, produce a report concerning the serious adverse event, and report immediately to the head of the institution and the investigational product provider. In addition, the principal investigator shall consider whether the case should be reported to the Minister of Health, Welfare, and Labor. If it is determined that it should be, it shall be reported to the Japan Agency for Medical Research and Development.

The head of the institution shall report to the Institutional Review Board upon receipt of a report by the principal investigator on a serious adverse event, and provide directions to the principal investigator regarding continuation of the trial based on the view of the Institutional Review Board.

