### Discontinuation of the Clinical Trial

The principal investigator and subinvestigators will take measures described below during the trial. If the trial itself is to be discontinued, the principal investigator and subinvestigators should maintain the safety of the subjects and take other appropriate measures. Reasons for discontinuation and any adverse events should be identified and recorded in the original documents and on the electronic case report forms. Tests and analyses that are scheduled at discontinuation will be performed as far as practical.

1) The Independent Data Monitoring Committee will be convened to review appropriateness of continuance of the trial, if adverse events of the following types occur: one or more serious adverse events regardless of causality; or two or more severe adverse events for which a causal relationship with the investigational products cannot be ruled out.

2) The clinical trial will be discontinued if serious adverse events for which a causal relationship with the investigational products cannot be ruled out occur during the trial and fall under either of the following conditions: two or more subjects aged below 18 experience severe adverse event(s); or a subject aged below 18 experiences three or more adverse events. The trial can be continued, however, if the Independent Data Monitoring Committee concludes that there is clear justification and means to maintain safety of remaining subjects.

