## Assembly of the Independent Data Monitoring Committee

[Calling committee meetings]

If any of the significant matters listed below occurs, the principal investigator will promptly request the chair of the Independent Data Monitoring Committee to call a committee meeting to review appropriateness of continuance of the trial and other related matters.

1) Discovery of new significant information on safety concerning the investigational products of the trial

2) Serious adverse events in the trial, regardless of causality

3) Recognition of new, significant information on safety derived from similar products, research reports, or other sources

4) Other matters that the principal investigator deems essential

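### A disease attack judged unrelated to the drug escapes serious adverse event reporting and automatic committee review, however serious it is

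*Protocol*

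**What the plan says.** Section 14.10.1 of the protocol opens with a broad definition of an adverse event that does not depend on causality. It then makes one exemption: "Exacerbation of the primary disease, including episodes, will not be regarded as an adverse event". Only one thing lifts that exemption, and it is a judgement on causality, not on seriousness. The clause reads: "with the exception of cases in which causal relationship with the investigational products cannot be ruled out".

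The later safety sections build on this definition:

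- Section 14.10.2 (Assessment of Adverse Events): "The items listed below will be examined and recorded on the electronic case report forms with regard to adverse events". Seriousness is one of those items.
- Section 14.10.3 (Definition of Serious Adverse Events) presents seriousness as a classification of adverse events. Its items include death, possible death, disability, possible disability and "Any case that requires hospitalization for treatment or prolongs the duration of hospitalization".
- Section 14.10.6 (Reporting of Serious Adverse Events) starts from the condition "If a serious adverse event is observed".
- Section 14.11.2 item 1 convenes the Independent Data Monitoring Committee for "one or more serious adverse events regardless of causality".
- Section 15.3 item 2 lists as a reason to call the committee "Serious adverse events in the trial, regardless of causality". Item 4 adds a discretionary reason: "Other matters that the principal investigator deems essential".

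**The concern.** Hearing loss and vertigo attacks are the expected events in this disease, and also the events through which harm to the inner ear would show. Exempting ordinary attacks is reasonable, because they are efficacy endpoints and are recorded daily. But the exemption has no override for seriousness. Whether a grave attack enters the safety system at all then rests on a single-case causality call, in a disease where attributing an attack to its natural course is easy.

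Safety and tolerability are the primary endpoints, and children are enrolled from age seven. What is at stake is the mandatory report and the automatic committee meeting for the most severe attacks.

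**Working it through.** The point turns on how the definitions connect. Take one attack that requires hospitalisation and follow it through the protocol under each causality judgement.

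| Step | Link to product not excluded | Link to product excluded |
|---|---|---|
| 14.10.1: adverse event? | Yes | No |
| 14.10.2 and 14.10.3: seriousness assessed? | Yes | No |
| 14.10.6: report mandatory? | Yes | No |
| 14.11.2 item 1 and 15.3 item 2: committee convened? | Yes | No |
| 14.11.2 item 2 and 15.5 item 1: can count toward stopping? | Yes, if the conditions on subjects under 18 are met | No, and would not even if it were a serious adverse event |

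Compare a hospitalisation for another illness, also judged unrelated. It is an adverse event, it is serious, it is reported, and it convenes the committee. The disease attack has the same seriousness and the same causality judgement, and does none of these.

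**Does any other provision restore the serious attack?**

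- Section 14.10.2 counts clinically significant abnormal test changes as adverse events, which might seem to catch a large audiometric loss. The specific exemption in 14.10.1 more naturally governs disease exacerbation, and 14.10.2 has no seriousness override.
- The section on Administration of Investigational Products suspends dosing for an unacceptable exacerbation. It requires neither a report nor a committee meeting.
- Section 14.11.1 item 8 allows withdrawal at the investigator's discretion.
- Section 15.3 items 1 and 4 allow the committee to be called for significant new safety information or other matters. Both depend on the investigator's view.
- Section 15.4 lets members ask for further information, but only once they are meeting.

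None of these makes a report or a meeting mandatory.

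**Which seriousness items should override the exemption?** Section 17.3.1 defines an audiometric episode as a change of at least 10 dB and counts ears and frequencies separately. The Background says the hearing loss can advance through its fluctuations. Item e) of 14.10.3, possible disability, could therefore be read to cover many ordinary episodes. Items a) to d) are not open to that reading, provided disability is taken as what persists after the episode.

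**Planned time under the rule** (sample size and visit weeks from the protocol):

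- All subjects, V1 to V13: 16 × 40/52 = 12.3 subject-years.
- Placebo run-in: 16 × 12/52 = 3.7.
- Placebo arm from V5 to V13: 4 × 28/52 = 2.2.
- Active arm from V5 to V13: 12 × 28/52 = 6.5, of which 12 × 24/52 = 5.5 is on drug.

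The protocol gives no rate of serious attacks judged unrelated. As an assumption only, let each subject have risk p of one. The chance of at least one among 16 subjects is 1 − (1 − p)^16: 15% at p = 1%, 56% at 5%, 81% at 10% and 97% at 20%. The range is too wide to size the gap.

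**The case against.** The strongest reply is that the exemption is deliberate and already guarded. Being unable to exclude a link is a low bar, and in Phase II the investigator does not know the arm or the trough level. A firm exclusion should be uncommon for a severe or unusual attack. This stands as a reason why the gap may be small. It does not close it, and exclusion is easiest in Phase I, where everyone is known to be on placebo.

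A reader might infer three stronger things that the documents do not support.

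- *That the stopping rules are weakened.* Section 14.11.2 item 2 and the event-based criterion in 15.5 item 1 count only events where a link cannot be excluded. An attack judged unrelated could meet neither, with or without the override.
- *That the protocol formally contradicts itself.* The triggers use serious adverse event as a defined term, and a carve-out in the definition is not a logical conflict. It does defeat the triggers' evident purpose for these attacks.
- *That serious attacks go unrecorded or cannot reach the committee.* Episodes are asked about daily (14.5), tested nightly (14.6) and followed by in-clinic audiometry at most visits (14.7.5). The investigator can call the committee under 15.3. The separate committee procedures mentioned in 15.1 are not shown and may add more.

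The objection that seriousness is also the investigator's judgement is fair. But under the present text that judgement is never asked for in an exempted attack.

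The objection that an override on every item of 14.10.3 could undo the exemption is right, because of item e). The override should be narrower.

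**Conclusion.** The concern holds in a limited form. An attack that is fatal, life-threatening, needs hospitalisation or leaves disability, and is judged unrelated, bypasses seriousness assessment, mandatory reporting and automatic committee review. What is lost is the report and the meeting, not a stopping criterion.

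The size is unknown because no rate is given. The trigger threshold is one event, so one such attack decides whether a meeting is mandatory. The conclusion assumes that 14.10.1 prevails over the test-result clause in 14.10.2, and that the committee procedures not shown do not already require such attacks to be reported.

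This is a cheap improvement worth making in a trial with safety as its primary endpoint. It does not show that the exemption itself is wrong.

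**What to change.** Keep the exemption for ordinary episodes and leave its causality exception as it is. Add one sentence to 14.10.1: an exacerbation or episode that meets 14.10.3 item a), b), c) or d) (death, possible death, hospitalisation or its prolongation, or disability persisting after the episode) is recorded and reported as a serious adverse event. It counts toward the committee-convening triggers in 14.11.2 item 1 and 15.3 item 2, whatever the causality judgement. Do not apply item e) automatically to fluctuating episodes.

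The cost is a few more serious-event reports and possibly an extra committee meeting. Sample size, endpoints and stopping criteria do not change.

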### Assessment of Adverse Events

The items listed below will be examined and recorded on the electronic case report forms with regard to adverse events that occur from the initial administration of investigational products (V1) to follow-up observations (V13).

If a diagnosis is settled based on signs or symptoms, the diagnosis rather than the signs or symptoms should be recorded. With regard to vital signs and clinical test measurements, changes from conditions before administration of investigational products should be assessed to determine whether the changes are clinically significant. An abnormal change that is considered clinically significant is to be counted as an adverse event. An abnormal change that is relevant to symptoms and signs already recognized as an adverse event, shall not be required to be newly reported as a separate adverse event.

・Name of the adverse event

・Date of occurrence

・Severity

・Seriousness

・Actions taken (administration of investigational products or other actions)

・Outcome and date of outcome confirmation

・Causal relationship with the investigational products

### Definition of Serious Adverse Events

Seriousness of adverse events is categorized as follows:

1) Non-serious: cases other than 2)

2) Serious: events for which any of the items from a) to g), below, apply.

a) Death

b) Cases that might result in death

c) Any case that requires hospitalization for treatment or prolongs the duration of hospitalization

d) Disability

e) Cases that might result in disability

f) Other medically serious condition for which seriousness is equivalent to a) to e), above

g) Any congenital diseases or abnormalities in the next generation

### Causality Assessment

Causality is categorized into “related” or “unrelated,” which are defined below. An adverse event that is considered to be “related” to the investigational products is regarded as a side effect.

[Criteria for judging causality]

| Causality | Description |
| --- | --- |
| Related | There is a reasonable possibility that the adverse event is related to the investigational products. |
| Unrelated | Conditions other than the above. |

### Severity of Adverse Event

Adverse events and severity of each adverse event will be assessed in accordance with the grades below.

[Grading scale for adverse events]

| Grade 1 | Mild; asymptomatic or mild symptoms; clinical or diagnostic observations only; or intervention not indicated. |
| --- | --- |
| Grade 2 | Moderate; minimal, local or noninvasive intervention indicated; or limiting age-appropriate instrumental activities of daily living (ADL)*. |
| Grade 3 | Severe or medically significant but not immediately life-threatening; hospitalization or prolongation of hospitalization indicated; disabling; or limiting self care ADL**. |
| Grade 4 | Life-threatening consequences; urgent intervention indicated. |
| Grade 5 | Death related to adverse event. |

*Instrumental ADL refers to preparing meals, shopping for groceries or clothes, using the telephone, managing money, etc.

**Self-care ADL refers to bathing, dressing and undressing, feeding self, using the toilet, taking medications, and not bedridden.

### Reporting of Serious Adverse Events

If a serious adverse event is observed, the principal investigator or subinvestigator shall take necessary measures such as treatment for the subject, produce a report concerning the serious adverse event, and report immediately to the head of the institution and the investigational product provider. In addition, the principal investigator shall consider whether the case should be reported to the Minister of Health, Welfare, and Labor. If it is determined that it should be, it shall be reported to the Japan Agency for Medical Research and Development.

The head of the institution shall report to the Institutional Review Board upon receipt of a report by the principal investigator on a serious adverse event, and provide directions to the principal investigator regarding continuation of the trial based on the view of the Institutional Review Board.

### Follow-up of Adverse Events

The principal investigator or subinvesigator will follow up all adverse events that occur during the clinical trial until the event has resolved or recovered to the state before the event, in principle. If there is a reasonable ground that justifies termination of the follow-up before completion, the principal investigator or subinvestigator will record the justification on the electronic case report forms on termination.

If an adverse event develops into a serious adverse event during the follow-up, the principal investigator shall report the situation promptly to the head of the institution and the investigational product provider, and act in accordance with Section 14.10.6, “Reporting of Serious Adverse Events.”

### Provision of Additional Information

1) If the principal investigator becomes aware of any information regarding serious and unpredictable side effects as stipulated in Article 80-2 (6) of the Law on Securing Quality, Efficacy and Safety of Products Including Pharmaceuticals and Medical Devices (Pharmaceuticals and Medical Devices Law) or Article 273 of the Enforcement Regulations of the Pharmaceuticals and Medical Devices Law, the principal investigator shall report the fact to the head of the institution and the regulatory authorities within the specified period.

The head of the institution will make a decision on whether continuation of the clinical trial is appropriate, after consultation with the Institutional Review Board. The principal investigator will provide updated information to the subjects in accordance with Section 8.4, “Revision of the Informed Consent Form.”

2) In addition to 1) above, the head of the institution will submit to the Institutional Review Board any report from the principal investigator concerning revision of the investigator’s brochure and the protocol, revision of the informed consent form, matters related to quality, efficacy, and safety of the investigational products, important information for appropriate operation of the clinical trial, and revision of other documents on matters to be discussed by the Institutional Review Board.

### Pregnancy during the Trial

If a subject or her partner is found to be pregnant or potentially pregnant, the principal investigator or subinvestigator will follow-up until delivery and assess the condition of the mother and child after the end of pregnancy, including delivery, as far as practical. If the subject herself is pregnant, administration of the investigational products to the subject will be immediately terminated. Unblinding of the emergency key code will be requested as appropriate.

## Discontinuation Criteria

### Participant Withdrawal

The principal investigator or subinvestigator will withdraw a subject from the trial if he/she meets any of the criteria listed below. On withdrawal of the clinical trial, the principal investigator or subinvestigator will immediately secure the safety of the subject and take appropriate measures. When a subject is withdrawn from the clinical trial, reasons for the withdrawal and occurrence of adverse events will be identified and recorded in the source document and on the electronic case report form. Tests that are scheduled at discontinuation will be performed as far as practical.

1) Subject’s request for withdrawal from the trial

2) Subject no longer trackable

3) Discovery of obvious ineligibility for participation in the trial

4) Decision of the principal investigator or subinvestigator that the subject’s participation in the trial would be difficult due to an adverse event that occurs after the initiation of the trial

5) Pregnancy of the subject

6) Death of the subject

7) Need for dosage reduction below the lowest standard of one 1-mg tablet every three days, administered orally

8) Other conditions that the principal investigator or subinvestigator deems appropriate for withdrawal

